### 3.2. Sub-Analysis (Longitudinal Changes in Antibody Detection)

Baseline detection of SARS-CoV-2 specific antibodies (IgG) will be summarized using descriptive statistics (counts and proportions for categorical data). HCWs with confirmed diagnosis with SARS-CoV-2 RT-PCR will be evaluated for the presence or absence of antibodies and the time interval between the two tests will be estimated. Durability of SARS-CoV-2 specific IgG antibodies will be assessed first by estimating the frequency (percentage) of the presence of antibodies and the mean (standard deviation) duration of persistence of the antibodies. Presence or absence of SARS-CoV-2 specific antibodies (IgG) (yes/no) at baseline will also be correlated with the disease severity.

Further, the nested cohort study will also provide additional answers regarding the durability of the humoral immune response. Baseline serology results of the 201 participants in the sub-study will be compared with the results of the subsequent serology test done at eight-week interval.

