A wide array of commercial and research SARS-CoV-2 antibody tests have been developed since the identification of the virus. They measure antibodies that target specific viral epitopes (nucleoprotein, spike protein, and receptor-binding domain) and measure immunoglobulin A, M, or G. IgG is the last antibody to rise in response to acute infection, but it persists the longest [11]. Serological testing includes lateral-flow antibody assays, beadbased assays (Luminex technology), enzyme-linked immunosorbent assays (ELISAs), and automated serology platforms. The two basic categories of serological tests currently available for COVID-19 are rapid diagnostic tests (also known as point-of-care tests) and formal laboratory serological tests. Rapid diagnostic tests often use the lateral flow design, which produces a color change on a test strip. The formal assays are either based on the ELISA or the chemiluminescent detection principle. At least three of these assays, available in South Africa, are produced by by Euroimmun, Roche Diagnostics, and Abbott Diagnostics.

A Cochrane review of 54 studies of laboratory and point-of-care assays reported pooled results for IgG/IgM sensitivity of 30.1% (95% CI 21.4–40.7) for 1 to 7 days, 72.2% (95% CI 63.5–79.5) for 8 to 14 days, and 91.4% (95% CI 87.0–94.4) for 15 to 21 days after the onset of illness. Between 21 and 35 days, pooled sensitivities for IgG/IgM were 96.0% (95% CI 90.6–98.3) [11]. Antibody testing is therefore only recommended after 14 days of symptoms in acute infection and has greater utility in late infection or to assess previous SARS-CoV-2 exposure or in seroprevalence surveillance.

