### 2.8. Oropharyngeal Swabs

Participants who report compatible symptoms (fever, cough, sore throat, loss of smell/taste, and shortness of breath) [1] at the time of the study will be offered oropharyngeal swab test for SARS-CoV-2 PCR. This will be captured separately in the research register as well as in the occupational health and safety (OHS) database for follow-up. Where there are gaps, the NHLS database and the Occupational Health Unit’s records will be reviewed for additional data.

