### 2.9. Possible Outcomes

SARS-CoV-2 serology results will be matched with the baseline results of SARS-CoV-2 RT-PCR if previously done.

The following categories will emerge:Both SARS-CoV-2 RT-PCR and SARS-CoV-2 serology are positive: COVID-19 diagnosis confirmed, and humoral immune response is present.SARS-CoV-2 RT-PCR is positive but SARS-CoV-2 serology is negative: COVID -19 diagnosis confirmed but there is no persistent humoral immune response or too early for antibody detection.SARS-CoV-2 RT-PCR not done or negative but SARS-CoV-2 serology is positive: COVID-19 diagnosis was missed by PCR but there is a humoral immune response present.Both SARS-CoV-2 RT-PCR and SARS-CoV-2 serology are negative: no confirmed infection with SARS-CoV-2.

All participants will receive their results within a month of the study from designated persons (Occupational Health Champions) at each study site. Additional interventions (clinical consultations and/or psychologist’s or Employee Assistant Programme practitioner’s referral) will be available for HCWs with specific needs.

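### The baseline durability percentage sets no minimum time from infection to blood draw, so PCR-positive staff bled before seroconversion would lower it

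*Protocol article*

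**What the plan says.** All references are to the protocol article.

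- **Section 3.2, group:** "HCWs with confirmed diagnosis with SARS-CoV-2 RT-PCR will be evaluated for the presence or absence of antibodies". The gap from PCR to serology is to be estimated as well, but nothing says what it is then used for.
- **Section 3.2, measure:** "Durability of SARS-CoV-2 specific IgG antibodies will be assessed first by estimating the frequency (percentage) of the presence of antibodies", together with a mean duration of persistence. Baseline presence or absence of IgG is also to be correlated with disease severity.
- **Section 2.9, second category (PCR positive, serology negative):** "COVID -19 diagnosis confirmed but there is no persistent humoral immune response or too early for antibody detection". Both meanings share one category.
- **Introduction:** "Antibody testing is therefore only recommended after 14 days of symptoms in acute infection". Pooled IgG/IgM sensitivity is given as 30.1% for days 1-7 after onset, 72.2% for days 8-14, 91.4% for days 15-21 and 96.0% between days 21 and 35.
- **Section 2.11:** the study assay is credited with 100% sensitivity at 17 days after symptom onset and 13 days after PCR positivity.
- **Section 2.8:** participants with compatible symptoms "at the time of the study will be offered oropharyngeal swab test for SARS-CoV-2 PCR", and of these swabs it says: "This will be captured separately in the research register".
- **Section 2.10:** only participants positive on both PCR and serology enter the nested cohort.
- **Section 2.12:** factors associated with durable IgG are a main outcome.

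**The concern.** A PCR-positive worker without detectable IgG may have lost antibody, may never have made it, or may have been bled before it could be detected. The last of these says nothing about durability, yet it lowers the percentage with IgG present exactly as a true loss does. The article recognises this when it defines the second category in section 2.9, but does not carry the distinction into the durability measure in section 3.2.

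The baseline percentage is the first durability measure, and the nested cohort is presented as adding to it. If recent infections are in the denominator, the percentage is partly a measure of how recently the PCR-positive staff were infected. The severity correlation uses the same mixed negatives, so time since infection can blur it. The same would hold for any analysis of factors for durable IgG that used baseline results.

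**Working it through.** **1. Is there a plan figure to reproduce?** No. The article gives neither an expected percentage with IgG present nor a share of PCR-positive staff bled early. The one calculated number nearby, the nested cohort size of 201, has no bearing on this point.

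**2. Does the text allow early draws into the percentage?** Section 3.2 names PCR-confirmed staff without a lower limit on the interval. Section 2.9 offers the too-early explanation for a negative serology, which is needed only if some PCR-positive staff are bled soon after infection. The Introduction and section 2.11 put reliable detection at more than 14 days after onset, or at 17 days after onset and 13 days after PCR for the study assay. None of these limits reappears in section 3.2.

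**3. How far could early draws move the percentage?** Let
- *f* = share of PCR-positive staff bled early (assumed; not in the article),
- *s_E* = probability of detectable IgG at an early draw: 0.301 (days 1-7) or 0.722 (days 8-14), from the Introduction,
- *s_L* = probability of detectable IgG at a later draw with no true antibody loss: 1.00 (section 2.11) or 0.96 (Introduction, days 21 to 35).

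Apparent percentage = *f* × *s_E* + (1 − *f*) × *s_L*. The shortfall due to timing alone is *f* × (*s_L* − *s_E*).

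With *s_L* = 1.00:

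| Assumed early share | Draws on days 1-7 | Draws on days 8-14 |
|---|---|---|
| 5% | 0.05 × 0.301 + 0.95 = 96.5% | 0.05 × 0.722 + 0.95 = 98.6% |
| 10% | 0.10 × 0.301 + 0.90 = 93.0% | 0.10 × 0.722 + 0.90 = 97.2% |
| 20% | 0.20 × 0.301 + 0.80 = 86.0% | 0.20 × 0.722 + 0.80 = 94.4% |

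The shortfall at 10% and 20% is 7.0 and 14.0 points for days 1-7, and 2.8 and 5.6 points for days 8-14.

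With *s_L* = 0.96:
- Days 1-7: 89.4% at a 10% share and 82.8% at 20%, so shortfalls of 6.6 and 13.2 points.
- Days 8-14: 93.6% and 91.2%, so shortfalls of 2.4 and 4.8 points.

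The choice of late sensitivity hardly changes the shortfall. The early share drives it.

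**4. Direction.** The percentage falls whenever *s_E* is below *s_L*. Only the amount is uncertain.

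**5. What is not touched.** The nested cohort admits only participants already positive on both tests, so nobody still awaiting seroconversion enters the eight-week comparison.

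**The case against.** The strongest reply is that the article is aware of the problem. It names the too-early reading in section 2.9, plans to estimate the PCR-to-serology interval, and never states an explicit denominator for the percentage. A condensed article may leave the handling of early draws to a fuller plan. The size is also open: the 10% and 20% shares are assumptions, PCR results come from the whole pandemic to date, and the early sensitivities are pooled over many IgG/IgM assays rather than taken from the study assay. If few staff were infected shortly before the survey, the effect is trivial.

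Much of this stands, and it limits the claim. It does not remove it, because section 3.2 does state a measure and a group, and the interval is not tied to either.

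Three stronger readings are tempting and are not supported:
- A reader might infer that staff swabbed at the survey are in the denominator. Section 3.2 would admit them and nothing excludes them. However, section 2.8 records those swabs separately, and section 2.9 matches serology to PCR tests done previously. Their status is unclear.
- A reader might infer that the plan equates a negative that is too early with antibody that is not durable. No section says so. The fault is that the distinction is not used in the percentage.
- A reader might infer that the main outcome on factors for durable IgG is biased. Section 2.12 does not say whether it rests on baseline results or on the nested cohort, so this is conditional.

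**Conclusion.** The point holds for the baseline durability percentage and the baseline severity correlation. As written, PCR-positive staff bled before IgG is reliably detectable would count as antibody-absent in a measure meant to describe durability, against the article's own statements on when serology is informative. With no true antibody loss, an assumed early share of 10% to 20% lowers the percentage by about 3 to 6 points for days 8-14 and about 7 to 14 points for days 1-7. This rests on the assumed share, on pooled sensitivities that are not those of the study assay, and on reading the denominator as all PCR-confirmed staff. Seroprevalence and the cumulative infection outcome are outside this point.

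**What to change.** 1. In section 3.2, restrict the baseline durability percentage, the severity correlation, and any durable-IgG factor analysis based on baseline results to PCR-positive staff bled beyond a stated interval consistent with the Introduction and section 2.11. One example is at least 17 days after symptom onset, or at least 13 days after the PCR date where there were no symptoms.
2. Also report the percentage by PCR-to-serology interval, so that the effect of the cut-off can be seen.
3. In section 2.9, split the second category into draws made too early, which are not evaluable for antibody response, and later draws with no IgG detected. Label the latter as lost or never formed, because a single negative result cannot separate the two.
4. State whether PCR positives identified at the survey visit are included.
5. Keep early cases as infected in the cumulative outcome of section 3.1.

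The cost is wording, since the PCR-to-serology interval is already to be obtained. The downside is that a few recent cases leave the durability denominator.

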Areas of uncertainty with SARS-CoV-2 antibody testing, is how long the IgG antibody levels remain detectable in the blood and the durability of humoral immune response post-infection. Early reports of serial antibody testing in recovering COVID-19 cases indicated an apparently short-lived antibody response. One study of 34 mild cases reported a half-life of 36 days for IgG levels measured over approximately 90 days [12]. In contrast, a recent seroprevalence study was performed on over 30,000 Icelanders, including 1797 RT-PCR confirmed COVID-19 cases, using six different antibody assays. This study demonstrated good IgG antibody durability, with levels rising to two months post-infection, and then sustained up to four months (the study cut-off) [13]. It is therefore unclear whether there are regional or ethnic variations in the durability of SARS-CoV-2 antibodies. The proposed study aims to estimate the cumulative SARS-CoV-2 infection rate and will further examine the durability of the humoral immune response specific to this virus in a cohort of HCWs in the Eastern Cape, South Africa.

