### 2.10. Nested Cohort Study (N_b_ = 201 Participants)

The sample size for the cohort study was estimated as 201 based on the expected proportion of HCWs (45% was reported in hospital setting in London by Houlihan et al. [2]) who could have acquired SARS-CoV-2 during the peak period of the pandemic. This sample was calculated at a 95% confidence level and confidence interval of 7.5. The final sample was adjusted in anticipation of a 27% attrition rate during the follow-up of the participants.

Only participants in category one will be pooled into the nested cohort study for serial antibody screening at eight-week interval to monitor the rate of decline in the antibody positivity rate (durability of SARS-CoV-2 specific humoral immune response). The participants in this sub-study will have blood samples drawn on two occasions; at baseline and final sample will be drawn at eight-week interval. Most studies have reported significant decline in the antibody levels by three to four months [12,13]. In anticipation of the challenges of follow-up study, participant recruitment will be based on their willingness to allow monitoring of their SARS-CoV-2 antibody levels. There will be no form of coercion of any HCW to participate or continue follow-up. Participants in this sub-study will receive text messages and face-to-face reminders on the date for blood tests.

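### Mean (SD) duration of antibody persistence cannot be estimated from one or two samples, and the nested cohort's eight-week loss is conditional on baseline seropositivity

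*Protocol article*

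**What the plan says.** Section 3.2 has two parts.

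- **Baseline part.** Workers with a PCR-confirmed diagnosis "will be evaluated for the presence or absence of antibodies and the time interval between the two tests will be estimated". Durability is then summarised by the percentage with antibody present and by "the mean (standard deviation) duration of persistence of the antibodies". Baseline presence or absence is also related to disease severity.
- **Nested cohort.** "Baseline serology results of the 201 participants in the sub-study will be compared with the results of the subsequent serology test", the repeat being eight weeks later.

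Section 2.10 sets the cohort's sampling and entry: participants have "blood samples drawn on two occasions; at baseline and final sample will be drawn at eight-week interval", and "Only participants in category one will be pooled into the nested cohort study for serial antibody screening at eight-week interval". Category one means both PCR and serology positive. Category two, PCR positive but seronegative, is read in Section 2.9 as meaning that "there is no persistent humoral immune response or too early for antibody detection".

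Section 2.12 lists factors associated with durable IgG among the main outcomes.

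**The concern.** A mean duration needs an observed start and an observed end. A PCR date can serve as the start, but the end is never seen:

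- people positive at their last test are right-censored;
- people who turn negative between the two samples are interval-censored within an eight-week gap;
- PCR-positive people already negative at baseline lost antibody at an unknown earlier time, never responded, or were tested too early.

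The plan nevertheless names a plain mean and SD. Readers would take the result as a biological persistence time, although it would largely describe when the survey was held. The Conclusions expect the durability findings to offer insight for vaccine research, so such a misreading would matter.

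The nested cohort raises a second, smaller issue. It starts with people who have kept their antibody up to baseline, so the fraction lost over the next eight weeks does not describe loss since infection.

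**Working it through.** **The plan's own figure.** The only number given for the sub-study is its size, 201. It reproduces as 1.96² × 0.45 × 0.55 / 0.075² = 169.0; with an unstated finite population correction for 2250, 157.3, rounded up to 158; then 158 × 1.27 = 200.7, so 201. It has no bearing on the duration estimator. The plan gives no expected persistence or seroreversion rate.

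**Inputs.** From Section 2.10: two samples, 56 days apart. Assumed, because the article does not give them: time t from PCR to baseline uniform on 60 to 150 days; persistence T lognormal with sigma 0.6 and median m, so true mean = m × exp(0.6²/2) = 1.197m. The article does not define how duration is calculated; here it is the time from PCR to the last positive test in category one.

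**Formula.** Category one is T > t. The recorded duration is t + 56 if T > t + 56, and t otherwise. Hence

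recorded mean = E[t | T > t] + 56 × P(T > t + 56 | T > t).

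However long antibody lasts, this cannot pass E[t] + 56 = 105 + 56 = 161 days for this window.

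**Results (1,000,000 draws per row).**

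| Median (days) | True mean (days) | Positive at baseline | Category one positive at 8 weeks | All PCR-positives positive at 8 weeks | Recorded mean (days) |
|---|---|---|---|---|---|
| 120 | 144 | 60% | 54% | 33% | 129 |
| 180 | 216 | 81% | 72% | 58% | 142 |
| 240 | 287 | 91% | 82% | 75% | 149 |
| 365 | 437 | 98% | 93% | 91% | 157 |

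Check of the first row: 98.3 + 56 × 0.544 = 128.8.

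**Survey date.** Moving the window to 90 to 180 days, with persistence unchanged, gives recorded means of 157, 169, 177 and 185 days, a shift of 27 to 28 days in each row. Tripling true persistence within the first window gives the same change: 157 − 129 = 28 days.

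**Other assumptions.**

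- Window of 30 to 270 days: the recorded mean runs from 137 to 193 days over the same four scenarios. This is more responsive, but still far from 144 to 437.
- Weibull persistence (shape 2), single-sample duration: raising the true mean from 120 to 480 days moves the recorded mean from 98 to 105, 126 to 134, or 154 to 164 days for windows starting at 60, 90 or 120 days. The SD stays near 24 to 26 days, close to that of the 90-day window itself (90/√12 = 26).

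**Nested cohort.** P(T > t + 56) = P(T > t) × P(T > t + 56 | T > t). At median 180 days, 0.809 × 0.717 = 0.580. The cohort sees the second factor (72% still positive); persistence since PCR is the product (58%). Under the Weibull with mean 240 days and window 90 to 180 days, loss is 22% in category one against 39% since PCR. In all nine Weibull scenarios the category-one loss was the smaller.

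**The case against.** The strongest reply is that a reader might infer that durability is estimated only in people still seropositive at baseline. The article does not support that. Section 3.2 evaluates all PCR-confirmed workers for presence or absence of antibody, so category two enters the percentage positive. That measure responds strongly to true persistence (60% to 98% in the table). The category-one restriction applies to the nested cohort alone.

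A reader might also infer that the factors found for durable IgG are biased towards durability. This has not been shown. The one association that Section 3.2 names, with severity, uses baseline presence or absence and so includes seronegatives, and the simulation contains no covariates.

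Three further points stand in part:

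- Loss over eight weeks among baseline seropositives is a legitimate quantity. The 72% and 58% answer different questions, and neither is a wrong estimate of the other.
- The magnitudes depend on a persistence distribution, a survey window and a definition of duration that the article does not give. This limits the size of the effect but not its direction.
- Censoring may be handled in a fuller document that is not shown. But the article does not merely leave the method open: it names a mean and SD, and that is the statement to correct.

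Section 2.10 also remarks that "Most studies have reported significant decline in the antibody levels by three to four months" and cites two studies, while the Introduction describes one of them as finding IgG "with levels rising to two months post-infection, and then sustained up to four months". That is a background inconsistency worth tidying. It is not part of the case against the estimator.

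**Conclusion.** The point holds in limited form and should be fixed. The mean (SD) duration is not identified by one sample, or by two samples eight weeks apart, and as written it would mostly report the PCR-to-draw interval. Under lognormal persistence and a 60 to 150 day window, a threefold rise in true mean persistence (144 to 437 days) moves it by 28 days, about as much as holding the survey 30 days later. The size is assumption-based. The direction follows from the sampling scheme, since no recorded duration can extend beyond the last test.

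The nested cohort's eight-week loss is valid as a quantity conditional on baseline seropositivity, and misleading only if presented as durability since infection. The baseline percentage positive and the primary seroprevalence analysis are not touched by either issue.

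**What to change.** 1. Delete the mean (SD) duration from Section 3.2.
2. Take the PCR-positive date as time origin and include all PCR-positive workers, categories one and two, with the baseline result and the eight-week result where there is one. Report the proportion seropositive by time since PCR, or an interval-censored time to seronegativity. A Turnbull curve or a parametric model would serve; the simpler tabulation is adequate.
3. Analyse separately those sampled under 14 days after PCR, because category two mixes waned responses with tests done too early. This fits the Introduction's advice to test only after 14 days of symptoms, and Section 2.11, which gives full assay sensitivity at 13 days after PCR positivity. It also deals with workers first swabbed at the study visit under Section 2.8.
4. Report eight-week seroreversion in the cohort of 201 as conditional on a positive baseline test.

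Cost: a change of wording and modest extra analysis. Section 3.2 already plans the PCR-to-serology interval and the baseline serology of PCR-confirmed workers, so no new samples are needed.

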### 2.11. Laboratory Testing

Serum samples will be run on the Abbott ARCHITECT *i*1000SR instrument using the Abbott SARS-CoV-2 IgG assay in accordance with the manufacturer’s instructions. This is a CLIA for the qualitative detection of IgG in human serum or plasma against the SARS-CoV-2 nucleoprotein. Strength of response in relative light units reflects quantity of IgG present and is compared to a calibrator to determine the calculated index (specimen/calibrator [S/C]) for a sample (with positive at 1.4 or greater). This assay was independently evaluated for analytic performance and found to have a specificity of 99.9% from 1020 pre-COVID-19 serum specimens and a sensitivity of 100% at 17 days after symptom onset and 13 days after PCR positivity [19].

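### The planned correlation of baseline IgG with disease severity names no adjustment for the PCR-to-serology interval, although that interval is already to be estimated and IgG detection depends on it

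*Protocol article*

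**What the plan says.** Section 3.2 plans several analyses of antibody detection. For workers with RT-PCR-confirmed infection, antibody presence will be evaluated and "the time interval between the two tests will be estimated". A later sentence adds the analysis at issue: "Presence or absence of SARS-CoV-2 specific antibodies (IgG) (yes/no) at baseline will also be correlated with the disease severity". No covariate or stratification is attached to it.

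Elsewhere the article treats IgG detection as dependent on time:

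- Section 2.9 interprets a positive PCR with negative serology as "no persistent humoral immune response or too early for antibody detection".
- Section 1 cites pooled IgG/IgM sensitivities by time from illness onset: 30.1% at days 1 to 7, 72.2% at days 8 to 14, 91.4% at days 15 to 21 and 96.0% between days 21 and 35.
- Section 1 also cites a study of 34 mild cases that "reported a half-life of 36 days for IgG levels measured over approximately 90 days", and a much larger Icelandic study with "levels rising to two months post-infection, and then sustained up to four months".
- Section 2.10 says: "Most studies have reported significant decline in the antibody levels by three to four months".

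Section 2.11 gives the result as a specimen/calibrator (S/C) index, "with positive at 1.4 or greater". Section 2.12 lists factors associated with durable IgG among the main outcome measures.

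**The concern.** A yes/no antibody result taken once, at enrolment, combines two things: whether the person mounted a response, and how long after infection the sample was drawn. Section 3.2 sets no minimum or common interval between PCR and serology. If severe and milder cases were infected, or had their PCR, at different times relative to sampling, that timing difference enters the severity association. It can look like a severity effect or hide a real one.

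The direction cannot be predicted. Later sampling of one group lowers its positivity through waning; very early sampling lowers it because IgG has not yet risen. Early samples are possible: Section 2.8 offers a PCR swab to participants with symptoms at the time of the study, and anyone positive then would have an interval near zero.

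Severity is the only candidate factor that Section 3.2 names in relation to antibody presence, so this result is likely to be read as an answer to the durability outcome in Section 2.12.

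**Working it through.** There is no stated sample size, power or effect for this analysis, so there is no figure of the plan to reproduce. The check asks how large the bias could be and when it vanishes.

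**Inputs from the documents:** positivity at S/C 1.4 (Section 2.11); IgG half-life *h* = 36 days, or no waning to four months (Section 1).

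**Assumptions, not in the documents:** 25% of cases severe; median S/C of 5 at day 21; standard deviation of ln(S/C) 0.9; interval with mean 90 and SD 35 days, never below 14 days; *h* = 70 days as an intermediate case; severe-minus-milder gap in mean interval of −30, 0 or +30 days.

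**Model with no severity effect:** ln(S/C) = ln 5 − ln 2 × (*t* − 21)/*h* + error, positive if S/C ≥ 1.4.

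**Closed form.** For a group with mean interval *m*, ignoring the 14-day floor,

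P(positive) = Φ{[ln(5/1.4) − ln 2 × (*m* − 21)/*h*] / √(0.9² + (35 × ln 2/*h*)²)}.

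For *h* = 36: ln(5/1.4) = 1.273, ln 2/36 = 0.01925, and the denominator is √(0.810 + 0.454) = 1.124.

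- Gap −30 (severe mean 67.5 days, milder 97.5): severe Φ[(1.273 − 0.895)/1.124] = Φ(0.336) = 0.632; milder Φ[(1.273 − 1.473)/1.124] = Φ(−0.178) = 0.429. Odds ratio = (0.632/0.368)/(0.429/0.571) ≈ 2.3.
- Gap +30 (severe 112.5, milder 82.5): severe Φ(−0.435) = 0.332; milder Φ(0.079) = 0.531. Odds ratio = (0.332/0.668)/(0.531/0.469) ≈ 0.44.

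**Simulation with the same inputs** (400,000 cases per scenario, logistic regression, no true effect):

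| Half-life | Unadjusted OR, gap −30 | Gap 0 | Gap +30 | Adjusted for interval |
|---|---|---|---|---|
| 36 days | 2.27 | 1.01 | 0.43 | 0.99 to 1.01 |
| 70 days | 1.67 | 1.00 | 0.60 | 0.99 to 1.01 |
| No waning | 1.00 | 1.02 | 1.02 | 1.00 to 1.03 |

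**False-positive rate** at nominal 5% (*h* = 36, severe cases sampled later, 2,000 repetitions): with 200 cases, 5%, 22% and 71% for gaps of 0, 15 and 30 days; with 400 cases, 4%, 43% and 93%. With the interval in the model the rates are 4.8% to 5.7% (200) and 4.4% to 5.0% (400). The two case numbers are also assumptions.

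**With a true two-fold severity effect on IgG level** (*h* = 36), the unadjusted odds ratio is 6.48, 2.70 and 1.19 for gaps of −30, 0 and +30 days. The adjusted value stays at about 3.6 to 3.7. At gap 0 the difference between 2.70 and 3.65 is not confounding: adding a covariate that predicts the outcome moves a logistic odds ratio away from 1.

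**Does another planned model cover this?** Section 3.1 plans multiple logistic regression. The outcome described there is a positive result on PCR, serology or both. That outcome equals 1 for every RT-PCR-confirmed worker, so it cannot estimate how IgG varies with severity among them. Time since infection is not named as a covariate anywhere.

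**The case against.** The text is silent on adjustment; it does not rule it out. A reader might infer that the investigators have chosen an unadjusted analysis. The article does not say so, and a condensed article commonly leaves covariates to a fuller document. Section 3.1 also refers to outcome measures in the plural, which could be stretched to include durable IgG. This stands in part. But Section 3.2 does specify an analysis, with its outcome form and its exposure, and derives the relevant time variable without using it there. The regression in Section 3.1 does not clearly reach it.

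Nothing in the documents shows that the interval differs by severity. The 36-day half-life comes from a small study of mild cases, and the larger study cited beside it found sustained levels. That stands: with equal intervals, or with no waning and no early samples, there is no false effect.

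It is tempting to state the size as a fold difference in the S/C index, for example 2^(30/36) = 1.78 for a 30-day gap. That is not the bias in the planned analysis, which is binary: a fall in index changes nothing for a participant who remains above 1.4.

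A reader might also infer that workers known to be infected only through serology, who are IgG-positive by definition, will distort the milder group. This holds only if they are included. An earlier sentence in Section 3.2 concerns RT-PCR-confirmed workers, so restriction to them is at least as natural a reading.

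Finally, a yes/no result is the assay's intended output, and this is one secondary association beside the frequency, duration and repeat-serology analyses of durability.

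**Conclusion.** The point holds as a low-cost improvement to a stated analysis. Section 3.2 names no adjustment for an interval that it will already estimate, while the article's own account makes a negative IgG depend on that interval. The bias is conditional: it needs the interval to differ by severity and IgG to wane or not yet to have risen.

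Its size cannot be known from the documents. The odds ratios of about 2.3 and 0.43 rest on the 36-day half-life, a 30-day gap and the assumed severe fraction, index distribution and interval distribution. At a 70-day half-life they shrink to 1.67 and 0.60; with no waning or no gap they are about 1.0. The illustration excludes samples before day 14, so it says nothing about the size of early-sampling bias. The documents do not support saying that the severity result will be wrong, only that the analysis as worded could not separate severity from timing.

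**What to change.** In Section 3.2, replace the correlation sentence with a specification along these lines: among RT-PCR-confirmed healthcare workers, baseline IgG positivity will be modelled by logistic regression on disease severity with the PCR-to-serology interval as a covariate, and the time-adjusted severity estimate will be the main result. Stratifying by interval is an acceptable alternative. Because IgG first rises and may later fall, the interval should be allowed a non-linear effect or entered in categories. Report the interval distribution by severity group, so that readers can see whether timing differed.

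Optional sensitivity analyses are a linear model of log S/C index, since "Strength of response in relative light units reflects quantity of IgG present", and exclusion of very early samples. Any early cut-off should state its starting point: the 14 days in Section 1 count from symptoms, not from PCR.

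The cost is slightly more analysis and no new data, because the interval is already to be estimated and the assay produces the index. The PCR date is only a proxy for the time of infection, so some residual confounding by time may remain and should be acknowledged.
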